**LIST OF ABBREVIATIONS**

| AIDS | Acquired ImmunoDeficiency Syndrome |
| --- | --- |
| ART | Antiretroviral Therapy |
| AYHIV | Adolescents and Youth with HIV |
| CATS | Child & Adolescent Trauma Screen |
| CMD | Common Mental Disorders |
| COVID-19 | CoronaVirus Disease of 2019 |
| cRCT | Cluster Randomized Control Trial |
| DALY | Disability Adjusted Life Year. |
| EQUIP | Ensuring Quality in Psychological Support |
| GAD-7 | Generalized Anxiety Disorder-7 |
| HIV | Human Immunodeficiency Virus |
| LTFU | Loss To Follow Up |
| NASCOP | National AIDS andSTI Control program |
| PCL-5 | Post Traumatic Stress Disorder Disorder Checklist 5 |
| PHQ-9 | Patient Health Questionnaire-9 |
| PRO-ACT | Psychoeducation, Relaxation, problem solving, Activation, Cognitive Therapy |
| PTSD | Post Traumatic Stress Disorder |
| TF-CBT | Trauma Focused Cognitive Behavioral Therapy |
| UHC | Universal Health Coverage. |
| WHO | World Health organization |

**PROTOCOL SUMMARY**

| **Title:** | Psychoeducation, Relaxation, PrOblem solving, Activation, Cognitive coping Therapy’ (PRO-ACT) for Adolescents and youth in HIV Care |
| --- | --- |
| **Objective:** | This study aims to adapt and evaluate a brief transdiagnostic psychological intervention (PRO-ACT) for adolescents and youth with HIV (AYHIV) for delivery by non-specialists; and determine contextual implementation factors and cost of implementation to inform scale-up. |
| **Aims:** | Aim 1: Adapt and optimize the delivery of PRO-ACT for HIV clinics serving AYHIV ages 16-24 years in Kenya  Aim 2: Evaluate the effectiveness and implementation of PRO-ACT for AYHIV ages 16-24 years in a cluster randomized trial  Aim 3: Determine cost of implementation for PRO-ACT training, delivery, and implementation process |
| **Methods** | Aim 1: Adaptation of PRO-ACT training and delivery will be conducted through a stakeholder-led process.  Aim 2: Effectiveness-implementation hybrid 1 cluster randomized controlled trial (cRCT). Optimization of PRO-ACT delivery will be done in 15 intervention sites after training of the non-specialist providers. We will use continuous quality improvement over a 6-months period.  Aim 3: Economic evaluation taking into account costs at various levels |
| **Population:** | Stakeholders: Policy makers, providers, adolescents and youth with HIV, caregivers, researchers  Health care workers: Currently employed in HIV care services  Patients: Adolescents and youth with HIV ages 16-24 years |
| **Number of Sites:** | 30 sites in Nairobi, Kisumu and Homa Bay counties in Kenya |
| **Study Duration:** | 5 years |
| **Outcomes** | Aim 1: Provider training   - Non-specialist providers’ competence to deliver PRO-ACT - Non-specialist providers’ satisfaction with PRO-ACT training   Aim 2: cRCT   - Primary Effectiveness Outcome: Reduction in depressive, anxiety and trauma symptoms among AYHIV - Secondary Effectiveness Outcome: Viral suppression among AYHIV - Implementation Outcomes: Reach, adoption, fidelity / implementation, maintenance, acceptability and appropriateness of PRO-ACT - Service Outcomes: Satisfaction with services by AYHIV and providers   Aim 3: Economic evaluation   - Cost of PRO-ACT provider training and implementation - Incremental cost-effectiveness: net added cost per case of depressive/anxiety/trauma symptoms resolved (health outcome) |
| **Primary analysis** | Effectiveness of PRO-ACT will assessed using 6-month analysis to provide an estimate of the near-term treatment effect, and at 12 months to examine treatment effect sustainability. The analyses will employ random coefficients models to account for clustered data structure, and compare outcome means separately (depression, anxiety, trauma) between the treatment and control groups. |

1. **BACKGROUND INFORMATION AND SCIENTIFIC RATIONALE**

**1a. Background Information**

Mental health is defined as a state of mental well-being that enables people to learn, work, cope with life stressors and contribute to their community.^1^ If an individual is unable to achieve this equilibrium, they face a challenge in using their abilities in accordance with accepted societal values.^2^ Such individuals find difficulty in recognizing, expressing and modulating their own emotions and use of basic cognitive and social skills in problem solving and coping with adverse life events. Over 900 million people around the world were living with a mental disorder in 2019, with anxiety and depressive disorders the most common.^3^ Due to the COVID-19 pandemic, this number rose significantly in one year, 2020 recording a 28% increase.^4^

Close to 25% of youth worldwide suffer from Common Mental Disorders (CMD) which include depressive and anxiety disorders, These disorders differ from fear and stress that any person can experience at some moment in life.^5^ The vast majority of these youth reside in resource limited settings.^6^ Mental health screening may help in early detection and intervention which allow for more effective pathways to be taken long before the problems commence or worsen.^7^ It also allows for tailoring interventions to specific populations.^8-11^. Transition from childhood to adulthood has registered a peak in incidences of mental health disorders, in five people; at least one has experienced clinically relevant mental health problems before attaining 25 years.^12^

Guidelines on promoting mental health among adolescents by the World Health Organization identify six main areas of focus among them, psychosocial interventions for Adolescents and Youth with HIV/AIDS (AYHIV) to prevent mental disorders, self-harm and other risky behaviours.^13^ Kenya has developed policies and guidelines for mental health care. The constitution of Kenya 2010 under chapter 48 outlines the rights of patients with mental health problems and gives modalities of establishing institutions that manage mental health in the national and devolved governments.^14^ National guidelines for provision of adolescent youth-friendly services in Kenya 2005 focused on the general wellbeing and reproductive health of youth with a very small portion on mental health.^15^ These guidelines were revised in 2016 with a goal of improving availability, accessibility and quality of healthcare for the adolescent and youth^16^ still with a major bias towards reproductive health and a small component of mental health.

During the COVID-19 pandemic, a comprehensive guideline on mental health and psychosocial support was developed by the ministry.^17^ The Ministry of Health Mental Health Policy 2015-2030 was developed with the following objectives; align mental health services to the constitution of Kenya, national and global health agenda; address the mental health challenges and trends and mitigate their burden; integrate mental health services within the Kenya Essential Package for Health (KEPH); and promote and respect rights of persons with mental health challenges.^18^

Kenya has 1.4 million people with HIV/AIDS, with a national prevalence at 4.9%, prevalence in women being 6.6% while men being 3.1%. The gender disparity among the youth is higher.^19, 20^ The top five high-prevalence counties are Homa Bay (~20%%), Kisumu (~18%), Siaya (~15%), Migori (~13%) and Busia (~10%)^20^. These counties and Nairobi County also have the highest burden of HIV among adolescents and youth^20^. New infections in Kenya are on an increase, for instance, young people (15–24 years old) contributed an estimated 12,000 infections (>50% of all adult infections) in 2021-2022.^20^

**1b. Significance and rationale**

*Mental disorders are a major cause of morbidity among adolescents and youth with HIV (AYHIV).^21^* Globally, approximately 3.5 million young people (age 15-24 years) live with HIV; 60% are girls, the majority (>80%) in sub-Saharan Africa (SSA).^22,23^ Improved survival of children due to successful roll-out of antiretroviral therapy and new infections in adolescence contribute to rising numbers of AYHIV. Kenya is a high HIV-burden country with nearly 150,000 young people living with HIV and 14,000 new infections annually.^24^ Vulnerability to HIV and mental health conditions intersect in adolescence and youth, a sensitive period of neuropsychological and social development during which individuals seek greater autonomy and initiate sexual activity.^25,26^ HIV is associated with mental health problems and decreased quality of life for adolescents and young people.^27-30^ AYHIV suffer from depression and anxiety disorders as they adjust to the diagnosis, adapt to life with a chronic, life-threatening disorder, experience stigma, and manage disease progression.^25, 31-33^ Several systematic reviews highlight the substantial burden of mental health problems facing AYHIV.^32,34-38^ Recent reviews report prevalence of any psychiatric disorder near 25%, anxiety 25-44%, and depression 25-50% among AYHIV. Studies in Kenya have documented similarly high rates of psychiatric morbidity among AYHIV, (prevalence of 50% for any psychiatric illness and depression).^39,40^ AYHIV rates exceed prevalence in the general population.^41-45^

*Modifiable correlates of mental disorders among AYHIV are well known and can form targets for intervention.*^32^ Community level factors (HIV-stigma and violence), family level factors (poverty, quality of parenting, and caregiver mental health) and HIV-related factors (rapport with healthcare providers and duration on ART) directly influence mental health.^46-50^ Older and behaviorally-infected HIV adolescents and youth have the highest rates of mental disorders and the lowest level of support from the health system due to health provider bias.^51^ Our group showed that 22% of Kenyan adolescents receiving care in a comprehensive HIV clinic in Nairobi changed homes in the past year and 30% missed a meal involuntarily, reflecting unstable social support and widespread poverty.^39^ As we pursue interventions to address these risk factors,^52-54^ there is an immediate need to address their effects on mental health.

*Mental disorders increase non-adherence to HIV care and viral non-suppression, which affect quality of life and mortality risk.*^55-58^ AYHIV with psychological distress, depression, anxiety and post-traumatic stress consistently have lower ART adherence, poor retention in care, and viral load non-suppression compared to those without these disorders.^59-61^ Depressive symptoms disrupt daily activities, reduce concentration, foster non-adherence, and increase poor HIV treatment outcomes. Together, HIV disease and depression weaken school performance,^62^ which can reduce future economic prospects. Ideally, adolescent mental health care helps prevent harmful social consequences in adulthood.^63,64^

*Effective depression treatments exist and have been linked to improvement in ART adherence.*^65-67^ Use of psychotherapy in addition to medication effectively improves depression and treatment adherence among AYHIV.^68^ In a recent meta-analysis, the odds of adhering to HIV care was 83% higher for those receiving care/interventions for depression or psychological distress.^65^ Integrating mental health and HIV services can help prevent new HIV infections and improve the health of people living with and affected by HIV by increasing access to coordinated care for people with complex conditions, enhancing provider communication, reducing stigma associated with seeking specialty care, and removing practical challenges of multiple care visits.^69-71^ Collaborative care models and task-sharing with peers, lay health workers, adherence counsellors, or other community-based human resources are useful strategies for administering evidenced-based psychosocial treatments in HIV affected communities in settings where mental health specialists are scarce.^72-77^

*SSA needs more practical, validated, scalable strategies to treat mental disorders among AYHIV.*^78,79^ Global targets require 90% of people with HIV linked to people-centered and context-specific integrated services by 2025.^80^ International and Kenyan HIV care guidelines call for psychosocial support for AYHIV, screening for depressive symptoms, psychotherapy for mild-moderate symptoms, and referral to mental health specialists for severe symptoms.^81-85^ However, weak systems, a paucity of competent providers,^78^ an overstretched workforce,^86-88^ and lack of a clear interface between HIV clinics and mental health specialists prevents guideline implementation.^89^

*Health care in Kenya is devolved with different mandates for the national versus county health systems.* The Kenya national Ministry of Health (MOH) is primarily tasked with policy development (including adolescent and mental health policies) and administrative oversight over vertical programs like the HIV program, the National AIDS/STI Control program (NASCOP). The national MOH also manages large tertiary health institutions including the major mental health hospitals located in large cities. Most Kenyans, however, seek care in county-level hospitals, managed by 47 different county administrations, charged with clinical service delivery, in-service provider training and implementation of programs^90^. A presidential taskforce on mental health in Kenya noted the glaring deficiencies in mental health care competency among providers in the county health facilities, and the need to devolve mental healthcare.^91^ This decentralization is a key component of universal health coverage (UHC), which Kenya is in the process of adopting.^92^

*Apart from a few medium to large well-funded HIV clinics in urban settings, integration of mental health within HIV services in Kenya is largely non-existent.* Kenya has insufficient mental health workers in public service for its population (100 psychiatrists, 500 psychiatrist-nurses), and the majority deliver specialist care in large facilities. Sub-county HIV clinics, where many AYHIV are managed, completely lack trained mental health personnel. In a typical HIV clinic AYHIV are not routinely evaluated for mental illness, but screening with the PHQ-9 may occur among AYHIV with non-suppressed viral loads. This may not lead to further assessment or referral due to inadequate clinician knowledge of the tool or lack of interface with specialists.

*The HIV program in Kenya offers an excellent platform to develop and study integration models for mental healthcare in routine care.* The HIV program in Kenya envisions integrating non-communicable disease care into routine HIV care, suggesting some readiness to accept innovations in this area. Kenya was among the first SSA countries to scale up comprehensive prevention of mother-to-child transmission,^93,94^ pediatric index-case testing,^95^ HIV self-testing and pre-exposure prophylaxis,^96^ and use of dolutegravir-based regimen.^97^ Additionally, the HIV program has experience with in-service provider training for patient-centric services^98,99^ and interventions involving task-shifting,^100^ making service provision more accessible to patients. Most HIV services are offered by non-specialist providers, including general medical officers, clinical officers, nurses and counselors without specialized training in psychology.^86^ Peer educators play a major role in care, especially treatment support for AYHIV.^101^ However, there are gaps that are amenable to targeted interventions. Routine screening and management of mental disorders is limited to a few well-resourced tertiary centers with trained mental health personnel.^91,102,103^ The scheduling of clinic visits for AYHIV to accommodate the school calendar may affect the implementation of mental health interventions.^104,105^ Our prior works shows that school-going youth attending boarding school make up 20% of AYHIV and they can only access mental health care on term and mid-term breaks. To address these challenges, there is an urgent need to integrate mental health services into the routine clinic visits for *all* AYHIV so that assessment and management of mild to moderate disorders and referral for severe symptoms occurs. To this end advances in modular, transdiagnostic psychological interventions hold great promise.

*Transdiagnostic interventions may be preferable to diagnosis-specific interventions*^106^ *in HIV care.* People with depressive, anxiety, or trauma disorders rarely present with ‘pure’ symptom criteria that align with a single diagnosis; rather, the conditions frequently co-occur.^107^ Thus, single-disorder-focused treatments may not match the more common clinical need.^108^ A meta-analysis of studies targeting youth for either depression or anxiety found a “cross over effect”: interventions targeting depression also reduced anxiety and vice versa, strengthening the case for transdiagnostic interventions.^109^

The Common Elements Treatment Approach (CETA) is a transdiagnostic psychotherapy developed by [name] and colleagues (Co-I on this proposal) that is based on common evidence-based treatments for depression, anxiety, trauma and stress-related disorders.^110,111^ CETA includes important advancements, but requires 8-12 sessions, making it difficult to integrate into HIV care for adults and school-going adolescents. A recent study in Mozambique using CETA for adults with HIV found that 80% achieved >50% reduction in symptoms in 6 or fewer sessions.^70,112^ The setback however was that only 14% completed treatment. This suggests a need for briefer transdiagnostic interventions like **‘Psychoeducation, Relaxation, PrOblem solving, Activation, Cognitive coping Therapy’ (PRO-ACT)** a brief trans-diagnostic intervention developed and piloted in Kenya among youth that can avoid high attrition due to length.^113^ Studies among adolescents and young adults in high-income countries have found brief psychological interventions effective.^114^ Only one study in an African country suggests that brief interventions for AYHIV may be preferable.^115^ Our pilot of PRO-ACT supports this finding. In the absence of adequate evidence on what works in integrated HIV care, the proposed study meets the need for the evaluation of brief transdiagnostic interventions that are effective and applicable for HIV services in low resource settings.^78^ This intervention will be particularly advantageous for adolescents and youth in school who cannot sustain lengthy programs.

*Quality of mental health care can be enhanced by assessing provider competency to target training and supervision.*^116^ The Enhancing Assessment of Common Therapeutic factors (ENACT) rating scale,^117,118^ used in the World Health Organization’s Ensuring Quality in Psychological Support (EQUIP) provider training platform,^119^ enables competency assessment by specialist or non-specialist (and peer) supervisors. ENACT consists of 15 core competencies, i.e., common factors among psychotherapies that influence client outcomes positively, and has been applied primarily in LMICs, where innovations in deployment of non-specialist mental health providers are more prevalent, given health system and community needs.^120^

1. **OBJECTIVES**

**2a. Study Objective**

This study aims to adapt and evaluate a brief transdiagnostic psychological intervention (PRO-ACT) for adolescents and youth with HIV (AYHIV) with delivery by non-specialists; and determine contextual implementation factors and cost of implementation to inform scale-up.

**2b. Specific Aims**

**Aim 1: Adapt and optimize PRO-ACT for HIV clinics serving AYHIV ages 16-24 years in Kenya**

Approach: With input from stakeholders, we will adapt and pilot PRO-ACT training and delivery for AYHIV in HIV clinics. Stakeholders include HIV/mental healthcare workers, policymakers, facility staff, and AYHIV. In collaboration with stakeholders, we will tailor implementation for the context (e.g., the specific cadre and when in the clinic visit mental health screening and management will be done).

**Aim 2: Evaluate the effectiveness and implementation of PRO-ACT for AYHIV ages 16-24 years.**

Approach: We will conduct a hybrid 1 effectiveness-implementation cluster randomized control trial in 30 HIV clinics. We will select and randomize 30 adolescent HIV clinics in Nairobi, Kisumu, and Homa Bay counties, and train non-specialist providers in 15 intervention sites. We will optimize the delivery of PRO-ACT in the intervention sites in a 6-month pretrial period using continuous quality improvement processes. Primary effectiveness outcome: Reduction in depressive, anxiety and trauma symptoms among AYHIV. Secondary outcome: Viral suppression among AYHIV. Implementation outcomes: Compare reach and describe adoption, fidelity / implementation, maintenance, acceptability and appropriateness. Identify determinants of reach, fidelity, and maintenance. Service outcomes: satisfaction of training by providers and satisfaction with services by AYHIV and providers.

*Hypothesis: The intervention will result in a significantly larger reduction of depressive, anxiety and trauma-related symptomatology over 12 months compared to the standard of care. Implementation of the intervention will improve the reach and maintenance in mental health screening and management for AYHIV.*

**Aim 3: Determine cost and cost-effectiveness of implementation for PRO-ACT training, delivery, and implementation process.**

Approach: We will conduct a time-driven activity-based costing of the intervention’s implementation strategies (training and implementation in clinics) within the 30 clinics in Kenya participating in the study to estimate the implementation costs from a patient and health system perspective. We will in addition utilize the health outcome data based on the health outcome of the intervention’s implementation in the 30 sites to estimate cost effectiveness or the intervention.

*Hypothesis: There will be an increase in costs related to the training and time for providers offering mental health services and a reduction in projected costs related to poor HIV-related and mental health. The incremental cost effectiveness ratio of the interventions will be positive.*

1. **STUDY OUTCOMES**

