| **Maintenance** | Screening for anxiety and depression | Proportion with sustained screening practices (% of AYHIV with a routine PHQ-2/9 at each visit) | Late (at month 12) implementation covering up to 12 months of adolescent treatment | Routine clinic patient records |
|  | Delivery of PRO-ACT intervention | Proportion with sustained treatment practices (% of AYHIV eligible for PRO-ACT with any PRO-ACT modules completed at each visit) |  | Checklist & patient records |
| **Acceptability** | Acceptability of PRO-ACT | Acceptability of PRO-ACT among AYHIV and providers in intervention clinics, assessed quantitatively and qualitatively | Early (month 3-6) and late (month 12) implementation and post-trial | Survey with HCW and post-trial FGDs and IDIs with HCW and AYHIV |
| **Appropriateness** | Appropriateness of PRO-ACT | Appropriateness of PRO-ACT among AYHIV and providers in intervention clinics, assessed quantitatively and qualitatively | Early (month 3-6) and late (month 12) implementation and post-trial | Survey with HCW and post-trial FGDs and IDIs with HCW and AYHIV |
| **SERVICE outcomes** | | | | |
| **Satisfaction with services** |  | Adolescent satisfaction with services received | Baseline and late implementation (at month 12) | Survey with enrolled adolescents |
| **Competency assessment** |  | ENACT assessment for providers | Pre-training, post-training, post-supervision | ENACT through EQUIP platform |
| **Self-efficacy** |  | Provider self-efficacy with implementing PRO-ACT | Baseline, month 3-6 and month 12 | Survey with HCW |
| **Provider satisfaction** |  | Provider satisfaction with services they offer, with the PRO-ACT training and supervision | Baseline, Post-training, and Post-supervision | Surveys with providers |

Aim 3: Economic evaluation

This aim will assess the following measures:

- Cost of PRO-ACT provider training and implementation
- Incremental cost-effectiveness: net added cost per case of depressive/anxiety/trauma symptoms resolved (health outcome)

*Additional exploratory outcomes*

- Cost per additional adolescent or youth with HIV with ≥80% adherence
- Cost per additional adolescent or youth with HIV virally suppressed

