***Economic evaluation of PRO-ACT***

*The unit costs* (relevant program and patient costs divided by outputs) will be calculated using a health system perspective as well as patients’ perspective. The costing approach will emphasize resources utilized, rather than out-of-pocket costs by including resources like donations or transfer payments as required. Costs for capital items will be amortized on a straight-line basis over their expected useful life, and assuming no salvage value. Facility space required for the intervention will be valued at the market rental rate. Outputs (denominator of the unit cost) include the numbers of patients receiving each type of study-supported services. We will assess the variation in unit costs across the study sites and identify the major determinants of that variation. We will compute the changes in unit cost over time as programs potentially achieve greater scale and administrative efficiency. We will also calculate the cost per additional AYHIV receiving mental health services.

*Estimating incremental cost-effectiveness:* This is the net added cost per case of depressive/anxiety/trauma symptoms resolved (health outcome). The numerator will reflect differences in the costs for the intervention arm and control arm. The denominator will represent the difference in the health outcome due to the clinical benefits of the intervention. The ratio is the incremental cost-effectiveness ratio (ICER) in dollars per health outcome.

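### The Aim 3 hypothesis that the ICER will be positive says nothing about cost-effectiveness, because the sign of the ratio does not separate good results from poor ones

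*Protocol*

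**What the plan says.** Section 2b of the Protocol gives Aim 3 as: "Determine cost and cost-effectiveness of implementation for PRO-ACT training, delivery, and implementation process". The hypothesis under it has two sentences. The first forecasts costs in both directions: "There will be an increase in costs related to the training and time for providers offering mental health services", and also "a reduction in projected costs related to poor HIV-related and mental health". It does not say which will be larger. The second is the only statement on cost-effectiveness: "The incremental cost effectiveness ratio of the interventions will be positive".

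Section 12c (Economic evaluation of PRO-ACT) defines the ratio. On top is the between-arm cost difference. Below it is the between-arm gain in health outcome credited to PRO-ACT. Of the quotient it says: "The ratio is the incremental cost-effectiveness ratio (ICER) in dollars per health outcome". The health outcome is a case of depressive, anxiety or trauma symptoms resolved, so a larger difference favours PRO-ACT. Section 3b and the Protocol Summary describe the same measure as a net added cost per resolved case.

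The Protocol gives no value per case resolved against which the ratio is to be judged.

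**The concern.** A ratio of two differences loses the sign of each. It is positive when both differences are positive and when both are negative. It is negative for the best result (cheaper and better) and for the worst (dearer and worse). A hypothesis stated as a sign therefore cannot express the claim that PRO-ACT is worth its cost.

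The same hypothesis also forecasts cost reductions without giving a net direction, so its two sentences can pull apart: a programme that saved more than it cost while resolving more cases would bear out the first and contradict the second.

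What is at stake is what Aim 3 can conclude. If the hypothesis is tested as worded, confirming it would not show cost-effectiveness and rejecting it would not show the opposite.

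**Working it through.** The Protocol states no cost difference, no difference in cases resolved and no ICER, so there is no figure to reproduce. The check is of signs, using the Protocol's own definition.

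**Definitions**
- dC = cost per patient, intervention minus control (numerator, section 12c).
- dE = cases resolved per patient, intervention minus control (denominator, section 12c; higher is better).
- ICER = dC / dE (section 12c).
- Incremental net benefit, for comparison: NB = L × dE − dC, where L is the value placed on one resolved case.

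**Assumed figures, for illustration only:** dC = ±100 dollars; dE = ±0.10, or 0.001, cases resolved per patient; L = 100, 500, 2,000 and 10,000 dollars per case. None of these is in the Protocol. The signs of the ICER do not depend on the sizes chosen.

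| Result | dC | dE | ICER = dC/dE | Hypothesis as worded | NB at L = 100 | 500 | 2,000 | 10,000 |
|---|---|---|---|---|---|---|---|---|
| Dearer, more effective | +100 | +0.10 | +1,000 | confirmed | −90 | −50 | +100 | +900 |
| Dearer, negligible benefit | +100 | +0.001 | +100,000 | confirmed | −99.9 | −99.5 | −98 | −90 |
| Cheaper, less effective | −100 | −0.10 | +1,000 | confirmed | +90 | +50 | −100 | −900 |
| Cheaper, more effective (dominant) | −100 | +0.10 | −1,000 | contradicted | +110 | +150 | +300 | +1,100 |
| Dearer, less effective (dominated) | +100 | −0.10 | −1,000 | contradicted | −110 | −150 | −300 | −1,100 |

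Worked entry: first row at L = 2,000, NB = 2,000 × 0.10 − 100 = +100.

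**Reading the table**
1. Rows 1 and 2 lie in the quadrant the authors most likely expect. Both confirm the hypothesis, although the cost per case differs 100-fold (100,000 / 1,000) and row 2 has negative net benefit at every L tried. This matters most, because it does not depend on an unexpected result.
2. Rows 1 and 3 give the same ICER from opposite findings on effectiveness.
3. Rows 4 and 5 give the same ICER, one for the best result and one for the worst. Net benefit is positive at every L for the first and negative at every L for the second.
4. Row 3 has positive net benefit at low L (+90 at 100). Net benefit alone therefore does not secure greater effectiveness, and a restated hypothesis should also require dE > 0.

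**The case against.** The strongest reply is that the sentence is a loosely worded expectation and does no work in the analysis. Much of this stands.

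- **No decision rule.** The sentence is labelled a hypothesis. A reader might infer that a positive sign would justify scale-up, so that an inferior programme could be rolled out on the strength of it. The Protocol does not support that: it says only that cost information will inform scale-up, and section 12c tests nothing against zero. Fewer cases resolved than under standard of care would also be inferior effectiveness, not necessarily harm.
- **Intended quadrant.** The phrase net added cost and the Aim 2 hypothesis of a larger symptom reduction show that dearer-and-better is expected. A less effective PRO-ACT would already contradict Aim 2. This makes the cheaper-and-less-effective case unlikely, but the wording does not exclude it, and within the intended quadrant the sign still carries no information.
- **The dominance case is conditional.** It needs the projected cost reductions to enter the numerator and to exceed the added costs. Section 12c does not say whether they enter. The cost sources listed in section 12a are expenditure records, facility interviews, time-and-motion studies and the patient survey, with no mention of projected savings. The case is open, not established.
- **The components will be known.** Numerator and denominator are each computed before division, so an analyst could identify the quadrant. That protects the reading of the results, but it does not repair the hypothesis.
- **Threshold and uncertainty methods.** Bootstrap intervals and acceptability curves may properly sit in an analysis plan, and their absence here is not a fault. The fault is a sentence that this Protocol does contain.

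**Conclusion.** The hypothesis is wrong as a statement about cost-effectiveness. In the expected quadrant it is confirmed at any cost per case. It is also confirmed by a cheaper, less effective result. It would be contradicted by a cost-saving, more effective one, if the projected reductions are counted and are large enough. The sign argument follows from the section 12c definition and needs no assumption about magnitudes; the dollar figures above are illustrations.

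The reach is limited. The ICER as an estimate, the primary outcome and the sample size are unaffected. A reader might go further and conclude that the economic evaluation as a whole is invalid; nothing in section 12c supports that, since the ratio is conventionally defined and its components are already planned.

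**What to change.** In section 2b, replace the second sentence of the Aim 3 hypothesis with a directional statement in two parts:

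- PRO-ACT resolves more cases than standard of care (incremental effect greater than zero); and
- PRO-ACT has positive incremental net benefit over a stated range of values per case resolved. Given the first part, this is the same as being dominant or having an ICER below the stated value.

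The study team must choose and justify the range, since the Protocol offers no figure for it. In section 12c, add that incremental cost and incremental effect are reported separately beside the ratio, and state whether the projected cost reductions named in the hypothesis enter the numerator. Methods for uncertainty can be left to the analysis plan.

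The cost is one replaced sentence and a short addition to section 12c. The two differences are already planned, and no new data are needed unless the team decides to count projected savings. The change is best made before any outcome or cost comparison between arms is seen.
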